## Discussion

This investigation responds to the urgent need to conduct rigorous research on policy and environmental approaches to obesity prevention. It has high public health significance, given the extent of the risks unhealthy dietary intake poses to children, especially those from systematically oppressed and minoritized backgrounds, who are most likely to participate in the NSLP. It also capitalizes on a unique natural experiment by systematically evaluating schools with and without salad bars in a large, diverse district.

The practice of installing salad bars, although intuitively appealing, has advanced well-ahead of the evidence. This investigation will make a significant contribution to policy research by providing the empirical data necessary to evaluate whether salad bars help achieve the HHKFA’s major goal of increasing FV intake within the NSLP [14]. It will also enhance understanding of the role of FVs and salad bars on energy intake at lunch in the NSLP. Moreover, results will identify consequences of and barriers and facilitators to salad bar implementation, including investigating how salad bars impact sales and NSLP participation, informing sustainability efforts. This application improves upon prior research in this area via its rigorous experimental design (RCT); large sample of students nested within matched schools; use of psychometrically sound, objective assessments of dietary intake by blinded assessors; consistent salad bar implementation; and a detailed analysis plan, all of which will minimize the influence of bias on results. Findings will be disseminated via policy briefs and to scientific, school, and community outlets. Only one prior RCT has prospectively examined the effects of salad bars on objectively assessed FV intake, and none has evaluated their effects on energy intake in school lunch. Examination of the potential moderating role of school-level sociodemographic factors further strengthens the significance of this application, enhances its external validity, [70] and will ultimately lead to targeted efforts to enhance dietary intake among children at greatest risk for obesity.

Since the initiation of this study, we have completed collection of Year 1 and the majority of Year 2 data, yielding > 14,000 images of school lunches. Data collection was paused in March 2020 when schools closed due to COVID-19, canceling post-ratings of one pair of schools scheduled to be rated that month. Students returned to school in Fall 2020, yet salad bars have not yet re-opened. The COVID-19 pandemic highlighted the critical role of school meals in addressing food security, and simultaneously placed enormous pressure on school nutrition programs to ensure students were fed [71]. When school buildings were closed in the Spring and Summer of 2020, schools set up meal distribution sites and delivery systems (all while understaffed and under-resourced). The return to school in 2020-21 brought new challenges related to increased demands for school meals, risk mitigation, staffing shortages, and supply chain disruptions. In response, the USDA issued national meal pattern waivers, allowing schools to veer from NSLP nutritional standards—including those related to milk, whole grains and sodium set forth by the HHKFA—and mandated universal free meals [71–73]. Many districts, including the one in this investigation, transitioned to more pre-packaged meals during this time and temporarily eliminated a la carte offerings. Although these temporary waivers helped schools meet the meal demands during that time, there is concern that diet quality has been compromised [71–73]. This is a particular concern given extension of nutrition waivers and the enhanced role of schools in addressing food security [71–73]. There is thus a great need to investigate how these changes have impacted children’s nutrition.

Given that surfaces are not the primary mode of COVID-19 transmission, and because a healthy diet is important to support immune functioning and overall health, some have argued that salad bars should return to schools [74]. However, it is unclear how potential barriers to the re-implementation of salad bars, such as staffing shortages and parents’ fears of the virus, might affect this process. Personal communication with this district’s Food and Nutrition Services stated plans to resume salad bar operations, yet acknowledged facing the same challenges as those encountered nationwide—adjusting to changes in school food policy mandates, supply chain disruptions, and staffing shortages. The resumption of data collection in the current application depends on timing of the return to salad bars in schools. Importantly, however, current estimates suggest that in our two years of data collection, we far exceeded projected numbers, even when removing data from the pair of schools for whom post-ratings were not conducted. To date, we have applied laboratory rating procedures on an estimated 11,000 school lunches across time points, from an estimated 5,500 students. Thus, even if data collection does not resume, we are optimistic that we will be adequately powered to respond to our study aims and hypotheses.

In sum, this study stands to be one of the most definitive investigations of school salad bars to date and will inform school nutrition policies and programming designed to enhance dietary intake and reduce obesity. The vital role of schools in promoting children’s nutrition and preventing food insecurity has become clearer to the nation since the onset of the COVID-19 pandemic, making this work particularly timely [71]. Future directions for this line of research include using these data, combined with results from our formative work, to design targeted interventions (adjunctive or alternative to salad bars) to optimize children’s FV intake within current school policy mandates.

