## Statistical analyses

### Power analysis

Power and effect size of the multilevel models that will be used to analyze the variety of outcomes in our cluster RCT are a function of a number of parameters: (1) the number of clusters (J = 16 independent schools [8 Intervention and 8 Control]), (2) the cluster size (*n* = 295 lunches per school), and (3) the ICC (estimated as 0.01, 0.05, and a much more conservative 0.10), which takes into account the correlated nature of our data and is the ratio of variability between clusters to the total variability [66]. Optimal Design Plus Empirical Evidence v3.01 software [67] was used to calculate the minimum detectable effect size given the parameters above, α = 0.05, and a desired power of 80%. For ICCs of 0.01, 0.05, and 0.10, we have 80% power to detect small to medium effect sizes of 0.17, 0.35, and 0.48, respectively. Thus, our proposed sample of 14,160 observations will be more than adequate to evaluate the study aims.

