### Analyses

Prior to analyses, distributions of all measures will be examined. Contingency tables and frequency distributions will be evaluated (for categorical and continuous variables, respectively), and transformations considered. Outliers will be checked for errors before being used in analyses. Sex differences will be assessed for all outcomes; if significant differences are found, analyses outlined below will be stratified by sex. All tests will be 2-sided at α = 0.05 level, corrected for multiple comparisons, and conducted in SAS v9.3.

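### The claim of adequate power without Year 3 rests on lunch counts, but the plan's own power method depends mainly on schools, and these fall from 16 to 11 or 12

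*Protocol article*

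**What the plan says.** The Power analysis section names three inputs: "the number of clusters (J = 16 independent schools [8 Intervention and 8 Control"]), "the cluster size (*n* = 295 lunches per school") and "the ICC (estimated as 0.01, 0.05, and a much more conservative 0.10"). With "α = 0.05, and a desired power of 80" per cent, it reports detectable standardized effects of 0.17, 0.35 and 0.48. The Analyses section adds that "All tests will be 2-sided at α = 0.05 level".

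The Design section reaches 16 schools over three years. Year 1 uses 8 schools. In Year 2 the four Year 1 controls become intervention schools and four new controls join. Year 3 repeats this step. The total is 12 pairs.

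The Discussion reports that Year 1 and most of Year 2 are complete, with COVID-19 closures "canceling post-ratings of one pair of schools scheduled to be rated that month". It then says that "we far exceeded projected numbers, even when removing data from the pair of schools for whom post-ratings were not conducted", cites about 11,000 rated lunches from about 5,500 students, and concludes that "even if data collection does not resume, we are optimistic that we will be adequately powered to respond to our study aims and hypotheses". This part of the Discussion gives no number of schools or pairs, no ICC and no recomputed detectable effect.

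**The concern.** The reassurance argues from lunches to power. In a trial that allocates schools, the between-school variance is divided by the number of schools, and more lunches per school do not reduce it. The article's own method has this property, and its Analyses section explains why clustering must be respected. Losing Year 3 removes four schools and four pairs, and the cancelled post-ratings remove a fifth pair. A surplus of lunches in the remaining schools cannot be assumed to make up for that.

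At stake is whether a two-year data set can be presented as sufficient for the study aims. A reader who accepts the sentence would take the detectable effects in the Power analysis section as still applying.

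**Working it through.** **Counts**

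- Years 1 and 2 use A1–D1, A2–D2 and A3–D3: 12 distinct schools and 4 + 4 = 8 pairs (Design).
- One Year 2 pair has no post-ratings (Discussion): 8 − 1 = 7 complete pairs, against 12 planned.
- The intervention school in that pair was a Year 1 control and so has baseline and post data from Year 1. Only the new control school lacks them. That leaves 12 − 1 = 11 schools with pre-post data, or 12 with any data, against 16 planned.
- Lunches: 11,000 / (7 pairs × 2 schools × 2 visits) = 11,000 / 28 ≈ 393 per school visit. The projection for those 7 pairs is 28 × 295 = 8,260. The three-year projection is 14,160.

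**Method**

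Two-level cluster-randomized comparison:

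SE = √{[ICC + (1 − ICC)/n] × (1/J₁ + 1/J₂)}, MDES = λ × SE,

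where λ is the noncentrality giving 80% power for a two-sided 5% t-test on J − 2 degrees of freedom: 3.013 for J = 16, 3.110 for J = 12, 3.150 for J = 11.

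**Reproducing the article's figures** (8 + 8 schools, n = 295)

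- ICC 0.01: 3.013 × 0.0578 = 0.174
- ICC 0.05: 3.013 × 0.1154 = 0.348
- ICC 0.10: 3.013 × 0.1605 = 0.484

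These match the stated 0.17, 0.35 and 0.48. A normal approximation gives 0.162, 0.323 and 0.450 and does not match, so the t-based form with school-level degrees of freedom is the one that fits.

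**Same method without Year 3**

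| Schools | Lunches per school visit | MDES at ICC 0.01 / 0.05 / 0.10 | Power at 0.17 / 0.35 / 0.48 |
|---|---|---|---|
| 16 (8+8) | 295 | 0.174 / 0.348 / 0.484 | 78% / 81% / 79% |
| 12 (6+6) | 295 | 0.208 / 0.414 / 0.576 | 63% / 66% / 65% |
| 12 (6+6) | 393 | 0.201 / 0.411 / 0.574 | 66% / 67% / 65% |
| 11 (6+5) | 393 | 0.213 / 0.437 / 0.610 | 61% / 61% / 60% |
| 12 (6+6) | unlimited | 0.180 / 0.401 / 0.568 | 76% / 69% / 66% |
| 11 (6+5) | unlimited | 0.191 / 0.426 / 0.603 | 71% / 63% / 61% |

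With 12 schools at ICC 0.05, going from 295 to 393 lunches moves the detectable effect only from 0.414 to 0.411. Even unlimited lunches do not bring it back to the stated value at any of the three ICCs.

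**Sensitivity to the design features that the formula ignores**

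Treat the analysis as a paired test of change with P pairs. Let s be the share of between-school variance that is stable from baseline to post. The article gives no value for s, so the range is assumed.

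SE = √{4 × [ICC(1 − s) + (1 − ICC)/n] / P}, on P − 1 degrees of freedom (λ = 3.367 for P = 7).

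Worked case, P = 7, n = 393, ICC 0.05, s = 0.5: √(4 × [0.025 + 0.00242] / 7) = 0.125; × 3.367 = 0.42.

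| s (assumed) | MDES with 7 pairs, ICC 0.01 / 0.05 / 0.10 |
|---|---|
| 0 | 0.29 / 0.58 / 0.81 |
| 0.3 | 0.25 / 0.49 / 0.68 |
| 0.5 | 0.22 / 0.42 / 0.58 |
| 0.7 | 0.19 / 0.34 / 0.46 |
| 0.8 | 0.17 / 0.28 / 0.38 |

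For comparison, 12 pairs with n = 295, ICC 0.05 and s = 0.5 give 0.30.

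**The case against.** Four points can be made for the article.

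- **The power formula is not the trial's analysis.** It is an unpaired comparison that ignores baseline, matching and the crossing of control schools into the intervention. The primary variable is change in FV intake in matched pairs. This stands: if roughly 70% of the school variance is stable, 7 pairs reach 0.35 and 0.48, and at about 80% they also roughly reach 0.17. With less stability they do not. The article gives no such figure, so its claim is left undetermined rather than supported. The 6+6 and 6+5 splits are likewise modelled on the article's 8+8 and are not the actual allocation.
- **The lunch-count statement is true in context.** It refers to two years with the incomplete pair removed: 11,000 against 8,260. This stands. Comparing 11,000 with 14,160 would misread the sentence. Only the step from that count to power fails.
- **The wording is hedged and no target effect is fixed.** This also stands in part. A reader might infer that the 80% power statement is false, or that the trial can no longer detect the effects it names. The documents do not support that: the 80% statement is tied to 16 schools and remains correct for them, and 60–67% power is reduced power, not inability to detect. Even so, the sentence is drawn as a conclusion from a premise that does not carry it.
- **A null result need not be misread.** A reader might infer that a null finding would be taken as evidence of no effect. Nothing in the article says so, and how null results are reported is commonly left to an analysis plan.

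Leaving detail to an analysis plan does not answer the main point, which concerns a claim that the article makes itself.

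**Conclusion.** The point holds in this form: the adequacy claim is unsupported by the article's own power method and inconsistent with it. On that basis, stopping after two years raises the detectable effects by about 15% to 27%. Relative to the unrounded planned values, the smallest rise is 0.201/0.174 = 1.15 and the largest 0.610/0.484 = 1.26; the article's rounded 0.48 gives 1.27 for the latter. The claim is not disproved for every effect: with 11 schools, true effects above about 0.44 (ICC 0.05) or 0.61 (ICC 0.10) would still have at least 80% power.

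The result assumes that the cancelled pair is the only Year 2 loss, that the 11,000 lunches belong to the 7 complete pairs, and that schools split nearly equally between arms. The lunch assumption matters little, as the unlimited-lunch rows show. The amount recovered through baseline and pairing rests on a school-level stability that the article does not report.

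**What to change.** In the Discussion, replace the inference from lunch counts with the number of complete pairs (7) and of schools (11 with pre-post data, 12 with any data), and with the recomputed detectable effect and power at ICC 0.01, 0.05 and 0.10. Better still, base the recalculation on the ICC and the pre-post school correlation estimated from data already collected, so that baseline adjustment and pairing are credited by a known amount. Otherwise drop the adequacy claim. The remark about exceeding projections may stay as a statement about two-year lunch counts, but not as a power argument.

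The cost is one recalculation, a few lines of text and a less favourable stated figure. No change to design or data collection is needed.

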## Data Availability

There are no data in this manuscript. Qualified individuals interested in study materials should contact the primary author ([name]).

## Abbreviations

NSLP: National School Lunch Program
FV: Fruits and Vegetables
